## Abstract

**Background:**

Parkinson’s disease (PD) is a neurodegenerative disease for which no disease-modifying therapies exist. Preclinical and clinical evidence suggest that repeated exposure to intermittent hypoxia might have short- and long-term benefits in PD. In a previous exploratory phase I trial, we demonstrated that in-clinic intermittent hypoxia exposure is safe and feasible with short-term symptomatic effects on PD symptoms. The current study aims to explore the safety, tolerability, feasibility, and net symptomatic effects of a four-week intermittent hypoxia protocol, administered at home, in individuals with PD.

**Methods/Design:**

: This is a two-armed double-blinded randomized controlled trial involving 40 individuals with mild to moderate PD. Participants will receive 45 min of normobaric intermittent hypoxia (fraction of inspired oxygen 0.16 for 5 min interspersed with 5 min normoxia), 3 times a week for 4 weeks. Co-primary endpoints include nature and total number of adverse events, and a feasibility-tolerability questionnaire. Secondary endpoints include Movement Disorders Society-Unified Parkinson’s Disease Rating Scale (MDS-UPDRS) part II and III scores, gait tests and biomarkers indicative of hypoxic dose and neuroprotective pathway induction.

**Discussion:**

This trial builds on the previous phase I trial and aims to investigate the safety, tolerability, feasibility, and net symptomatic effects of intermittent hypoxia in individuals with PD. Additionally, the study aims to explore induction of relevant neuroprotective pathways as measured in plasma. The results of this trial could provide further insight into the potential of hypoxia-based therapy as a novel treatment approach for PD.

**Trial registration:**

ClinicalTrials.gov Identifier: NCT05948761 (registered June 20th, 2023).

## Introduction

Parkinson’s disease (PD) is a chronic and progressive neurodegenerative disorder for which only symptomatic treatments are currently available. The pathophysiology of PD is complex and involves multiple mechanisms, including mitochondrial dysfunction and oxidative stress. Although there have been significant advances in understanding the molecular and cellular mechanisms underlying PD, disease-modifying therapies that can halt or slow down the disease progression are lacking [1]. Therefore, there is an urgent need for novel therapeutic strategies that can provide symptomatic relief and neuroprotection.

Recent preclinical studies have suggested that moderate hypoxia, the condition of low oxygen availability, may offer a promising non-pharmacological treatment avenue in PD [2]. Hypoxia activates evolutionarily well-preserved adaptive mechanisms that enhance neuronal viability and survival [3, 4]. Several animal studies have reported neuroprotective effects of hypoxia in neurodegenerative and mitochondrial disease models [5–9]. One potential mechanism through which hypoxia treatment may improve PD is via the activation of the Hypoxia Inducible Factor 1 (HIF-1) pathway. HIF-1 is a transcription factor that plays a crucial role in cellular adaptation to hypoxia by regulating the expression of genes involved in energy metabolism, angiogenesis, and neuroprotection [10–12]. Short-term activation of HIF-1 may lead to increased nigrostriatal dopaminergic activity [13–16], while long-term repeated exposure to moderate hypoxia may improve the systemic tolerance of cells and tissues to subsequent more severe stimuli, a process called hypoxic conditioning [2, 11, 17]. Interestingly, HIF-1 is necessary for the disease-modifying effect of exercise in preclinical substantia nigra models [18]. Intermittent hypoxia - the interspersion of hypoxia with brief periods of normoxia – therefore seems a promising method of administration as it allows for recovery and prevents tolerance to the hypoxic trigger [2, 19]. Several intermittent hypoxia studies have been conducted in elderly and fragile populations [20–25], and in a previous phase I study, we have demonstrated the safety and feasibility of hypoxia trials in individuals with mild to moderately severe PD (manuscript in preparation).

In this phase 1b-2a randomized controlled trial, we aim to investigate the safety, tolerability, feasibility, and net symptomatic effects of a four-week intermittent hypoxia protocol at participants’ homes. Mechanistic effects are explored by investigating putative neuroprotective blood markers. We hypothesize that a remote intermittent hypoxia protocol in individuals with Parkinson’s disease is (1) safe and feasible in individuals with PD without cardiorespiratory comorbidity and that a 4-week protocol (2) improves symptomatic and functional outcomes, and (3) increases hemoglobin, hematocrit and induces markers of neuroprotection.

## Study objectives

### Primary objective

(i) to explore the safety (number and nature of AEs) and feasibility and tolerability (questionnaire) of remote administration of intermittent hypoxia interventions in PD.

### Secondary objectives

(ii)to explore the net effects of a 4-week intermittent hypoxia protocol on a battery of standardized and functional scales, including Movement Disorders Society-Unified Parkinson’s Disease Rating Scale parts II and III.(iii)to assess the net effects of a 4-week intermittent hypoxia protocol on plasma biomarkers, indicative of neuroprotective pathway induction.

### Methods/Design

#### Design

We will study the safety and net effects of a 4-week intermittent hypoxia protocol in a two-armed randomized controlled trial. The design and content of several elements of the current study is based on a previous exploratory phase I multiple N-of-1 trial [26]. 

### Population

We will include 40 individuals with PD, clinically confirmed by a movement disorders-specialized neurologist.

**Inclusion criteria**.

Able and willing to provide written informed consent.Clinical diagnosis of Parkinson’s disease by a movement disorders-specialized neurologist.Hoehn and Yahr stage 1 up to and including 3.

### Exclusion criteria

An individual who meets any of the following criteria will be excluded from participation in this study:

Individuals with a diagnosis of restrictive and obstructive pulmonary diseases, cardiac output deficits, sleep apnea (or signs or symptoms thereof), excessive alcoholic intake, congestive heart failure and coronary artery disease NYHA classes III and IV.Arterial blood gas abnormalities at screening procedure (see limits and stop criteria in *Supplementary Materials*).Individuals with shortness of breath or other airway or breathing-related inconvenience related to lack of dopaminergic medication.Unable to come to the clinic for measurements in OFF phase, or having unstable dopaminergic medication.Individuals with active deep brain stimulation (DBS).

#### Sample size calculation

As this involves a phase 1b-2a trial with no previous comparable insights to base a calculation upon, formal sample size calculations will not be possible. Similar to our previous hypoxia trial [26], *n* = 20 per treatment arm is considered sufficient to assess nature and number adverse events, as well as the feasibility (Appendix III) of performing a hypoxia trial remotely.

#### Recruitment and consent

Individuals with PD will be recruited from a national recruitment website for PD-related research (*ParkinsonNEXT.nl*). Participants will receive an e-mail with detailed information on the study, including an overview of time investment and risks of participation. Individuals will have a consultation by telephone with the study contact person to answer questions about the research after receiving the information. If the participant is still interested, a screening questionnaire will be sent before the physical screening procedure. The coordinating investigator will contact the participant before in-clinic screening procedure if potential exclusion criteria are met, to prevent any unnecessary participant visits. Before the on-site screening begins, the informed consent form is signed.

### Premature termination of participants

Participants have the right to withdraw consent at any moment during the study period without any consequences. After withdrawal, subjects will not be replaced during the study. Follow-up of withdrawn participants will be conducted by telephone consultation within one week after the last intervention. The occurrence of adverse events will be evaluated actively on a weekly basis. If permitted by the participant, the reason for study withdrawal will be collected.

### Premature termination of the study

Informed by our phase I study, we do not expect to terminate this study on the basis of adverse events. However, the study will be terminated or be put on hold if the intervention appears to be harmful or if serious adverse events occur probably or definitely due to trial interventions. Any issue regarding study continuation will be discussed in close consultation with the Data Safety Monitoring Board (discussed hereafter).

### Interventional medical device

A commercially available hypoxic generator (*b-Cat ALT-120*, B-cat High Altitude, Tiel, the Netherlands) is used, which is similar to devices regularly used in hypoxic training studies [26–38]. The intervention will be primarily administered at the participant’s home. Therefore, the generator is modified in collaboration with the manufacturer, such that the device automatically titrates the correct fraction of inspired oxygen (F_I_O_2_) of 0.16 in a closed feedback loop with an F_I_O_2_ sensor, and automatically regulates the intervention per protocol (five times five minutes hypoxia interspersed with five minutes of normoxia, totaling 45 min). This protocol was selected based on (1) the balance between safety and clinical effects as derived from our first study [26] (manuscript submitted), (2) the literature on the spectrum of dose-related effects of intermittent hypoxia [19], and (3) the multidimensional respiratory dysfunction in PD in response to (severe) hypoxia observed in our previous study (manuscript submitted), limiting the intensity of the hypoxic stimulus as per our current stop criteria (*Appendix I**I*).

The participant wears a pulse oximeter that feeds back to a computer linked to the generator. When SpO_2_ drops below 80% or SpO2 input is lost for one minute, the device automatically switches off and defaults to room air. As an extra safety measure, a safety button needs to be pressed every couple of minutes in response to a flashing light signal by the participant during any intervention. When the button is not pressed, the device switches off and the participant breathes room air. Lastly, a continuous output oxygen measurement system verifies appropriate dosing. Other device settings that are normally customizable are now disabled or moved to the inside of the machine and can therefore not be reached or modified by the participant. This will increase the safety of using the hypoxicator in the home environment. Participants receive elaborate on-site instructions and a tailored instruction manual for own use. A technical schematic of the device and its safety modifications is added in *Appendix I**V*.

### Outcomes and measurements

#### Primary outcomes: safety and feasibility

This is the first trial that investigates the deployment of an intermittent hypoxia protocol in a remote setting. In our previous trial, we tested single sessions of different hypoxia training protocols in PD (manuscript submitted). Building on that experience, the safety, tolerability and feasibility of a month-long intermittent hypoxia protocol in PD are the primary outcomes of this study (Table 1).

**Table 1 Tab1:** Co-primary and secondary outcome measures

Co-primary study outcomes	Remarks
Adverse events	Number and nature
Feasibility and tolerability questionnaire (*Appendix I**II*)	Categorized as per a widely used feasibility framework [49]. Items in each category (e.g. acceptability, expectancy) were subsequently inspired by a variety of healthcare feasibility questionnaires.
**Secondary study outcomes**	
Movement Disorder Society-Unified Parkinson’s Disease Rating Scale (MDS-UPDRS) part II and part III score	Experiences limitations in activities of Daily Living (part II, participant-reported) and Examination of motor symptoms (part III, clinician-assessed)
Purdue pegboard test (PPT)	Left hand, right hand, both hands
Timed Up & Go Test (TUGT)	Time and number of steps, average of two trials
Six-minute walking test (6MWT)	Distance covered
Parkinson’s disease questionnaire-39 (PDQ-39)	Self-completed
Accelerometry-measured resting tremor and pronation-supination	Movisens® Move 4 activity sensor
Plasma markers of target engagement and blood biomarkers	Hemoglobin, neurofilament light chain (NfL), clusterin, GFAP, UCH-L1, BDNF (brain-derived neurotrophic factor)

### Secondary outcomes: functional and motor tests

The selection of motor and functional outcome measures is based on the findings of our previous hypoxia trial (manuscript in preparation) and aims to measure for the first time the net symptomatic effects of a one-month intermittent hypoxia protocol in PD [26]. To the existing motor test battery, we added the MDS-UPDRS part II and 6-minute walking test (Table 1) to better account for functional effects, including exercise capacity.

### Secondary outcomes: plasma biomarkers

Plasma biomarkers are included as hypothesis-generating outcome measures and are based on their value in target engagement (hemoglobin, hematocrit) and sensitivity to either exercise and longitudinal disease progression.

Neurofilament-light chain (NfL) is associated with motor decline in PD [39, 40] and is reduced by exercise [41]. Clusterin is a potential important regulator of exercise effects, and might positively influence neuro-inflammation and be inversely associated with cognitive function [42–45]. Glial fibrillary acidic protein (GFAP) and ubiquitin carboxy-terminal hydrolase L1 (UCH-L1) are acute biomarkers of brain injury and might therefore give influence in whether this is upregulated in response to hypoxia as a stressor [46]. Brain-derived neurotrophic factor (BDNF) is potentially upregulated by hypoxia and exercise [47, 48]. As research into PD plasma biomarkers keeps accelerating, novel insights will be used to modify this preliminary biomarker selection. Extra plasma will be stored for additional analyses where appropriate. Any necessary protocol amendments will be coordinated with the medical-ethical committee.

### Other study parameters

In addition to the outcome measures, information about age, gender, disease severity (Hoehn and Yahr scale), disease duration, levodopa equivalent daily dose (LEDD) and use of concomitant medication (including any changes during trial participation) are collected.

### Measurement frequency

In-clinic measurements will be performed at baseline, in the week after the 4-week intervention period and 4 weeks after the last intervention session, except for the feasibility questionnaire that will be sent once, immediately after the intervention period. Adverse events are evaluated on a weekly basis.

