#### Intervention procedures

Interventions will be conducted three times a week, for four weeks in total. The first intervention will take place in the hospital under supervision of a pulmonary technician. Any subsequent intervention will take place at home, with a pulmonary technician present for instructions and monitoring at least once. If necessary for safety purposes, this technician will be additionally present for one or more subsequent interventions. After that, remote expert assistance is present through a live (video)call during each session in the first intervention week. Supervision can be extended when necessary for safety during subsequent weeks. Mandatory weekly videocalls ascertain adequacy of administration, safety and compliance. Participants are explicitly encouraged to spread the three interventions over any week as much as possible. By exception, an occasional intervention on the day following a previous intervention will be allowed.

Before the first session, the pulmonary technician will explain the working mechanism of the machine and will give ample time for questions. This includes the auto-off function of the machine, and when to contact the study team. When one individual has completed the Intervention phase, the machine will be collected and will be delivered to the next participant. In-between, machine parts that are part of the breathing circuitry will be cleaned for re-use.

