### Statistical analysis

#### Primary study outcomes

Safety (i.e., number and nature of adverse events) and the feasibility (i.e., questionnaire (details)) will be analyzed using descriptive statistics.

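### Co-primary feasibility is defined only by a self-report questionnaire that records no session completion or retention, so a favourable result is compatible with poor home delivery

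*Protocol article*

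**What the plan says.** The definition is the same throughout the protocol article.

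- **Abstract, Methods/Design:** "Co-primary endpoints include nature and total number of adverse events, and a feasibility-tolerability questionnaire".
- **Primary objective:** "to explore the safety (number and nature of AEs) and feasibility and tolerability (questionnaire) of remote administration of intermittent hypoxia interventions in PD".
- **Sample size calculation:** feasibility is followed by a pointer to Appendix III.
- **Table 1:** besides adverse events, the only co-primary entry is the "Feasibility and tolerability questionnaire".
- **Statistical analysis, Primary study outcomes:** "the feasibility (i.e., questionnaire (details)) will be analyzed using descriptive statistics".
- **Measurement frequency:** clinic measures are taken at three time points, "except for the feasibility questionnaire that will be sent once, immediately after the intervention period".

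Information on delivery appears elsewhere, but not as an outcome.

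- **Intervention procedures:** "Mandatory weekly videocalls ascertain adequacy of administration, safety and compliance".
- **Interventional medical device:** if saturation falls below the set limit or the oximeter signal is lost for a minute, "the device automatically switches off and defaults to room air". A missed press of the safety button also switches it off.
- **Premature termination of participants:** people who withdraw are not replaced. They are followed up by telephone, and their reason is recorded if they allow it.

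**The concern.** Hypothesis (1) in the Introduction is that a remote protocol is safe and feasible. The Discussion presents home administration as the main novelty and ties it to scalability and long-term compliance. Whether people at home actually carry out the sessions is central to that claim, and the chosen measure cannot show it. A participant who finished 4 of 12 sessions and one who finished all 12 could return identical answers.

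Sessions that end early are foreseeable, because the device has three separate triggers for switching itself off. Stopping because of a side effect may surface among the adverse events. Stopping because of burden, signal loss or missed button presses need not surface in either co-primary outcome. At stake is whether later trials can rely on this one as evidence that home delivery works.

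**Working it through.** **No figure to reproduce.** The article gives 20 per arm without a calculation. It states no drop-out rate, no feasibility threshold and no definition of a favourable questionnaire result. The check is therefore a reading of the instrument, followed by an illustration.

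**1. What the instrument covers.** Appendix III has 16 statements:

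- discomfort, mask breathing, fear, claustrophobia, fatigue, tedium, pain and duration (8 items);
- headache, shortness of breath and nausea (3 items);
- tolerance of longer exposure, feeling safe at home, wanting hospital staff present, recommending it to others, and whether the treatment seems logical (5 items).

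Sum: 8 + 3 + 5 = 16. Items on sessions started, missed, cut short or abandoned: 0.

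**2. Planned delivery.** Three sessions a week for four weeks gives 3 × 4 = 12 per participant, and 20 × 12 = 240 per arm. Intervention procedures places the first session in hospital, so at most 12 − 1 = 11 are at home, or 20 × 11 = 220 per arm. None of these counts enters the feasibility outcome.

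**3. Illustration for one arm of 20.** Assumptions: k participants stop early and do not return the questionnaire, and 90% of responders are favourable.

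- Figure among responders: 90% for every k.
- Over all randomised, stoppers counted as unfavourable: 0.90 × (20 − k)/20.
- Over all randomised, stoppers counted as favourable: 0.90 × (20 − k)/20 + k/20.

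| k | Responders | Stoppers unfavourable | Stoppers favourable |
|---|---|---|---|
| 2 | 90% | 0.90 × 18/20 = 81% | 81% + 10% = 91% |
| 3 | 90% | 0.90 × 17/20 = 76.5% | 76.5% + 15% = 91.5% |
| 5 | 90% | 0.90 × 15/20 = 67.5% | 67.5% + 25% = 92.5% |

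**4. The same in whole participants, with exact (Clopper-Pearson) 95% intervals.** Here every responder is favourable, and stoppers are assumed to leave halfway, after 6 sessions. Sessions delivered = 12(20 − k) + 6k.

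| k | Responders favourable (lower limit) | Completed and favourable, all randomised | Sessions delivered |
|---|---|---|---|
| 2 | 18/18 = 100% (81.5%) | 18/20 = 90% (68.3 to 98.8%) | 228/240 = 95% |
| 4 | 16/16 = 100% (79.4%) | 16/20 = 80% (56.3 to 94.3%) | 216/240 = 90% |
| 6 | 14/14 = 100% (76.8%) | 14/20 = 70% (45.7 to 88.1%) | 204/240 = 85% |

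The questionnaire result does not move while completion falls. Even if every stopper did return the form, the sessions column would still be absent from the outcome.

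**The case against.** The strongest case against is that the article is condensed, that the primary aim is exploratory and descriptive with no success rule attached, and that adherence and retention could be reported anyway. The abstract says the co-primary endpoints include the two named measures. Compliance is checked weekly, reasons for withdrawal are sought, and the interim analysis covers study progress. Table 1 also bases the questionnaire on a published feasibility framework, which cannot be judged from here.

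Part of this stands. Delivery will not go wholly unobserved, and with no decision rule the point is not critical. The appeal to condensation does not stand. The analysis section says what feasibility is, and the objective, sample size section and Table 1 agree. An adherence summary added later would fall outside the co-primary outcome as written.

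Several stronger readings are tempting but unsupported.

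- **That the answers come mainly from people who coped.** The article does not say withdrawn participants are denied the questionnaire. For someone who stops, the end of the intervention period could mean their own last session. The article is silent, which is a gap and not proof of selection.
- **That the device already records completion and shut-offs.** The device section describes real-time control and verification of output oxygen. It does not mention stored logs or causes of shut-off.
- **That all 12 sessions are at home.** The first is in hospital, and a technician attends at least one of the home sessions.
- **That the questionnaire is mere opinion.** Headache, nausea, breathlessness and pain are symptom reports and legitimate tolerability data, though all are self-reported.

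**Conclusion.** The concern holds in this form: co-primary feasibility rests solely on self-report, none of the 16 items captures delivery, and adherence and retention are not outcomes. This follows from the text and needs no numerical assumption.

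The size of any distortion cannot be known. The 81%, 76.5% and 67.5% depend on an assumed 90% favourable rate, an assumed 2, 3 or 5 stoppers, non-response by all of them, and the worst-case rule of counting each as unfavourable. Under the opposite rule the figures are 91% to 92.5%. The plan defines no favourable proportion, so these figures show the mechanism and do not predict a result.

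A reader might infer that the trial cannot answer its main question. That goes too far: adverse events and self-reported tolerability are still measured, and the objective is exploratory. What would lack support is a claim that the protocol can be delivered at home. This should be fixed, but it does not invalidate the design.

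**What to change.** Extend co-primary feasibility in the objective, Table 1 and the analysis section. Report it descriptively, by arm, over all randomised participants:

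- (a) sessions started and sessions fully completed out of 12 planned, with the home sessions (at most 11) shown separately from the in-hospital first session;
- (b) retention to the end of the intervention;
- (c) sessions ended by automatic shut-off, by cause if device data or the weekly calls allow it. The sponsor should confirm what can be retrieved.

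Keep the questionnaire as the measure of acceptability and tolerability. State that it is sent at the end of the intervention or at early stopping, whichever comes first, and report how many in each arm returned it. A completion threshold is optional in a descriptive trial; if one is used, fix it before any unblinded look.

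Items (a) and (b) should cost little, since compliance is already checked weekly and withdrawals are followed up. Item (c) may need some extra recording. The price is slightly more reporting and a feasibility figure that may look less favourable. No dose, schedule or stopping rule changes.
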